## Methods

### Study design and setting

This is an open-label, prospective, two-arm parallel RCT with balanced randomization (1:1), allocation concealment, and outcome assessment blinding. The study protocol employs the Standard Protocol Items: Recommendations for Interventional Trials (SPIRIT) guideline and the Consolidated Standards of Reporting Trials (CONSORT) statement for clinical trial transparency (29). The trial will be conducted at the Fujian Geriatrics Center, which is the largest geriatrics specialty among general hospitals in Fujian Province, China. Participants will be recruited from the *Fujian Prospective Aging Cohort* according to the screening criteria and randomly allocated to two groups: the *PF-Life* program (intervention) group and the health education (control) group. Data from each participant group will be collected at four different times: screening assessment, post-randomization baseline assessment, 4-month outcome assessment, and 12-month outcome assessment. The flowchart of the study protocol is displayed in Figure 1.

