#### Exercise program

The exercise program is based on and expands upon the standardized LiFE program (21, 38). It is a multi-component exercise program that incorporates four basic functional areas: aerobic conditioning, muscle strengthening, flexibility, and balance training. When designing content, each exercise was specifically chosen to be relevant to daily living activities in the home environment and was easy to incorporate or mimic daily life, such as lifting the toes and heels, chair rise, back scratch, simulated towel wringing, farmer’s walk, etc.

There are 16 sets in the three levels of difficulty based on functional performance: elementary, intermediate, and advanced with increasing complexity. Personalized exercise programs are customized based on the assessment of the participant’s current level of FF in endurance, balance, flexibility, and strength. The exercise programs follow the principle of progression, increasing the exercise load by adding more repetitions and longer training times and using ankle weights at higher levels. For example, the first month of strength training begins with 3 reps per set for 3 sets at 30% one repetition maximum (1RM) loading and progresses in the second month with a gradual progression to 5 reps per set for 3 sets at 80% 1RM. Frequency, Intensity, Timing, and Type (FITT) are based on the FITT Guidelines for Older Adults (39). Participants are advised to train five times a week at their preferred time for 16 weeks. After 16 weeks, participants may continue to use the program for as long as they choose. In addition to the multicomponent exercises, participants are encouraged to increase daily PA and decrease sedentary time through visual charts showing daily PA progress. The exercise program was developed by the research team in consultation with experts in geriatrics, sports medicine, and rehabilitation medicine. The instructional videos were filmed in advance and embedded in the mHealth platform.

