#### Implementation of the technology

Participants access the exercise program through the *PF-Life app*. The exercise tasks menu on the main interface present participants with a personalized list of exercises for each week. Tapping accesses the exercise task details, and participants perform the exercises while watching videos on the app. After completion of each exercise, feedback on the participant’s performance is captured on their smartphone and sent to healthcare professionals. Participants access visualized PA data uploaded by the wearable device, ActiGraph wGT3X-BT, as well as task completion, task progress bar, and exercise ranking, for self-monitoring. At the same time, participants use the app to communicate and interact with healthcare professionals via text, voice or video.

The *PF-Life* web portal is designed for healthcare professionals. Healthcare professionals customize exercise programs for each participant through the exercise task features and exercise parameters, and other data are transferred directly to the participant’s smartphone. The web portal allows healthcare professionals to view data from participants’ wearable devices and smartphones, monitor participants’ exercise progress, and make timely adjustments. In addition, healthcare professionals are reminded to intervene when exercise tasks are not completed by sending reminders or motivational text messages. Exercise completion is automatically recorded by the *PF-Life* app during intervention and follow-up, and PA data are uploaded from the wearable device (ActiGraph wGT3X-BT) and synchronized with the *PF-Life* web portal. Healthcare professionals assess and record participants’ adherence to the exercise program by monitoring their physical activity data (the number of days exercised per week, number of sets exercised per day, and the duration of exercised per set). Figure 2 shows screenshots of the main application features and representative functions of the *PF-Life* Platform.

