### Outcome measures

Table 1 provides a detailed summary of primary and secondary outcome measures for each assessment time point. Data collectors will be blinded to group assignments.

**Table 1 tab1:** Overview of primary and secondary outcomes, outcome measures, and assessment time points.

Outcomes	Outcome measures	Screening	Baseline	16 weeks	1-years
Eligibility assessment	Inclusion criteria	√			
	Exclusion criteria	√			
Primary outcomes					
Pre-frailty assessment	Fried frailty phenotype	√	√	√	√
Secondary outcomes					
Body composition	Body mass index, body fat mass, body fat percentage, fat-free body mass, fat-free mass percentage, and visceral fat level	√	√	√	√
Bone mineral density	Bone mineral density	√	√	√	√
Functional performance assessment	30-s chair rise test	√	√	√	√
	30-s arm curl test	√	√	√	√
	Hand grip strength	√	√	√	√
	Chair sit and reach test	√	√	√	√
	Back scratch test		√	√	√
	Timed up and go test		√	√	√
	Single-leg stance test		√	√	√
	4-m gait speed test		√	√	√
	2-min step test		√	√	√
Physical activity level assessment	Sedentary time (min/d), energy expenditure (MET/h), LPA (min/d), MVPA (min/d)		√	√	√
Inflammatory cytokines	Chemokines (CXCL8/IL-8, CCL5/RANTES, CXCL9/MIG, CCL2/MCP-1, CCL11/Eotaxin and CXCL10/IP-10, CCL4/MIP-1β, CCL7/MCP-3, CXCL1/GROα, CCL3/MIP-1α, CCL28/CTACK, and CXCL11/SDF-α)		√	√	√
	Cytokines (IL-2, IL-3, IL-4, IL-5, IL-6, IL-7, IL-9, IL-10, IL-12, IL-13, IL-15, IL-16, IL-17A, IL-18, IL-1β, TNF-a, TNF-β, IFNγ, and IFNα)		√	√	√
Exploitative outcome assessment	Medical and demographical data	√	√	√	√
	Sustainability		√	√	√

√, data will be obtained; MET, metabolic equivalents of task; LPA, low physical activity; MVPA, moderate-to-vigorous physical activity.

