### Primary outcome assessment

The primary outcome is the proportion of participants with pre-frailty in the intervention group compared with the control group over 12 months from baseline, as measured by the Fried frailty phenotype, which is currently an internationally recognized standard for frailty identification and assessment. The frailty criteria have five components (29): (i) unintentional weight loss (>4.5 kg or at least 5% of body mass in the previous year through a self-reported questionnaire); (ii) low handgrip strength (HGS, cutoff points: ≤30 kg for males and ≤18 kg for females); (iii) fatigue [self-reported using questions 7 and 20 of the Centre for Epidemiological Studies Depression Scale (CES-D)]. Study participants are asked how often in the past week they think they have had difficulty completing daily tasks and how often they have been unable to complete activities. A positive response of ‘most of the time’ or ‘always’ to either question is considered an indication of fatigue; (iv) slow gait (≥0.65 m/s walking speed over a 4.5 m distance); and (v) low PA levels (<383 kcal/week for males and <270 kcal/week for females). The presence of one or two of the five components is recognized as pre-frailty.

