#### Demographic and other baseline characteristics

Participants’ demographics (age and gender), socioeconomic attributes (marital status, education level, and average monthly income), lifestyle (smoking habits and alcohol consumption), and comorbidity will be collected through a structured questionnaire to prevent the influence of confounding factors such as demographics and other baseline variables on the results.

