### Statistical analysis

All data will be processed and analyzed using IBM SPSS 22.0 statistical analysis software, and a significance level of 5% will be used. Independent *t*-tests or *Mann–Whitney* tests will be used to compare demographic and other baseline characteristics of participants pre-intervention. A two-way ANOVA test with repeated measures for each of the variables will be applied to assess the effect of the program at pre-intervention, post-intervention, and follow-up stages on complexity (non-linear measures) vs. traditional (linear) measures of the proportion of pre-frailty, BC vs. BMD, PA vs. sedentary behaviors, FF (4-m gait speed test, TUG test, chair sit and reach test, back scratch test, single leg stance test, HGS, and 30-s chair rise test), and inflammatory cytokines. A subgroup analysis of the intervention group will be conducted after 12-month follow-up to explore the potential impact of continued exercise on the sustainability of the intervention effects. Multiple equation chain interpolation (MICE) is used to handle missing data, and where missing data are associated with observed covariates, propensity scores may be used to weight observations or adjust models to balance groups defined by missing data status. Statistical analyses will be performed using per-protocol and intent-to-treat (ITT) analyses in the case of potential dropouts.

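### The exploratory continued-exercise analysis rests on a self-selected split of the intervention arm and can show a difference, in either direction, when continuing has no effect

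*Protocol article*

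**What the plan says.** The analysis is announced in one sentence of the Statistical analysis section: "A subgroup analysis of the intervention group will be conducted after 12-month follow-up to explore the potential impact of continued exercise on the sustainability". The Exercise program section says how continued exercise comes about: "After 16 weeks, participants may continue to use the program for as long as they choose".

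Exposure is recorded as "the number of days exercised per week, number of sets exercised per day, and the duration of exercised per set" (Implementation of the technology). That section also says that the app logs exercise completion in both the intervention and follow-up periods. Outcome visits are the "4-month outcome assessment, and 12-month outcome assessment" (Study design and setting), and Table 1 schedules the Fried phenotype at baseline, 16 weeks and 1 year. Week-16 status is therefore known before the optional period begins.

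Two sentences touch on adjustment. In the Statistical analysis section, "propensity scores may be used to weight observations or adjust models to balance groups defined by missing data status". In the section on demographic and baseline characteristics, data are collected "to prevent the influence of confounding factors such as demographics and other baseline variables on the results". Neither mentions continuation or week-16 response.

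Table 1 places sustainability under "Exploitative outcome assessment", evidently meaning exploratory. The primary outcome is a between-arm contrast, "compared with the control group over 12 months from baseline".

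**The concern.** The analysis concerns what continued exercise does, but the participants themselves decide who continues, after randomization and after the week-16 result has emerged. Someone who has improved by week 16, or who was fitter throughout, is plausibly more likely to continue and also more likely to be free of pre-frailty at 12 months. The Background supports this: it lists poor exercise tolerance and lack of motivation among the barriers to exercise in pre-frail people.

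Without a control for week-16 status, the contrast mixes any effect of continuing with the reasons for continuing. A spurious result could be reported as evidence that continuing maintains the benefit, or that it does not.

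**Working it through.** **The plan's own figure.** The protocol gives no number for this analysis. The inputs come from its sample-size calculation, which reproduces. For 10% versus 40%, a two-sided Fisher test at 0.05 and 90% power, full enumeration gives 47 per arm (power 0.906; 46 per arm gives 0.898). Then 47/0.80 = 58.75, rounded up to 59 per arm, or 118 in total, as stated.

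**Inputs from the protocol.** Reversal in the exercise arm is 40%, taken here as the week-16 rate. The intervention arm has 70 participants and dropout is 20%, so 70 × 0.80 = 56 are evaluable.

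**Inputs assumed.** The protocol gives no rate of continuing or of 12-month status by week-16 response. Write c₁ and c₀ for the probability of continuing among week-16 reversers and non-reversers, and s₁ and s₀ for the probability of being robust (not pre-frail) at 12 months. Because s depends only on week-16 status, continuing has no effect by construction.

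**Formulas.** The share already reversed at week 16 is
- among continuers, r_C = 0.4c₁ / (0.4c₁ + 0.6c₀)
- among stoppers, r_S = 0.4(1−c₁) / (0.4(1−c₁) + 0.6(1−c₀))

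The spurious difference in 12-month status is (s₁ − s₀)(r_C − r_S). The spurious difference in change from week 16 is the same quantity minus (r_C − r_S).

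**Middle scenario (c 0.7/0.4, s 0.7/0.15).**
- Continuers: r_C = 0.28/0.52 = 53.8%; robust at 12 months (0.28×0.7 + 0.24×0.15)/0.52 = 0.232/0.52 = 44.6%; change −9.2 points.
- Stoppers: r_S = 0.12/0.48 = 25.0%; robust at 12 months (0.12×0.7 + 0.36×0.15)/0.48 = 0.138/0.48 = 28.8%; change +3.8 points.

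| Scenario | c₁/c₀ | s₁/s₀ | r_C − r_S | 12-month status, continuers minus stoppers | Change from week 16, continuers minus stoppers |
|---|---|---|---|---|---|
| Milder | 0.6/0.4 | 0.6/0.15 | 0.500 − 0.308 = 0.192 | 0.45 × 0.192 = +8.7 points | 8.7 − 19.2 = −10.6 points (unrounded) |
| Middle | 0.7/0.4 | 0.7/0.15 | 0.538 − 0.250 = 0.288 | 0.55 × 0.288 = +15.9 points | 15.9 − 28.8 = −13.0 points (unrounded) |
| Stronger | 0.8/0.3 | 0.8/0.1 | 0.640 − 0.160 = 0.480 | 0.70 × 0.480 = +33.6 points | 33.6 − 48.0 = −14.4 points |

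Within a stratum of week-16 status both differences are zero. Everyone in a stratum starts from the same status, so comparing level or change no longer matters.

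**False-positive rate.** Simulation with no effect of continuing used 20,000 replicates per scenario, 40% reversal, continuation from 60/40 to 80/30 and 12-month rates of 60/20, 70/10 or 80/10. An unadjusted Fisher test of continuers against stoppers on 12-month status was compared with a Cochran–Mantel–Haenszel test stratified by week-16 response.
- n = 70: unadjusted 7.9% to 80.5%; stratified 4.5% to 5.1%.
- n = 56: unadjusted 6.4% to 68.7%; stratified 4.1% to 5.0%.
- Continuation unrelated to response (50/50): unadjusted 3.4% to 4.0%, so no inflation.

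**Limit of the adjustment.** Among responders only, suppose an unmeasured health factor drives both continuation (70/30) and persistence (90/50). The Fisher test then rejected in 9.6% of trials, against 2.8% without that factor.

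**Precision.** In the middle scenario 56 participants split into about 0.52 × 56 = 29 continuers and 27 stoppers, with (0.232 + 0.138) × 56 ≈ 21 robust at 12 months. The standard error of the crude difference is √(0.446×0.554/29 + 0.288×0.712/27) ≈ 0.127, a 95% half-width of about 25 points.

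**The case against.** The case for leaving the plan alone has four parts.

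- **Sustainability does not depend on this analysis.** A reader might infer that the subgroup is the trial's answer on durability. The documents do not support that: the primary outcome is a randomized contrast over 12 months, and the repeated-measures analysis includes the follow-up stage. The long-term effects promised in the abstract are those of the programme, not of continuing it. This stands, although the randomized contrast cannot isolate the effect of continuing.
- **It is exploratory.** The wording and Table 1 both say so. This stands and lowers the weight. The label does not remove the bias from the estimate.
- **Silence is not a decision to leave it unadjusted.** The article states neither the groups, the outcome scale nor the covariates, and a full protocol or SAP may do so. This stands: it would be wrong to read the article as rejecting adjustment. Continuers against stoppers is the natural reading, but the article does not spell it out. What it does state is the self-selected split and the aim of learning the impact of continuing.
- **The direction is not fixed.** A reader might infer that the result must favour continuing. It need not: with change from week 16 as the outcome the sign reverses, and maintenance among week-16 reversers shows no difference in these scenarios. This stands. It shows that the answer can depend on an outcome definition the article leaves open.

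**Conclusion.** The point holds as a minor to moderate one. The split is post-randomization and self-selected on the article's own words, and the only propensity weighting it names serves missing data. With no effect of continuing, the contrast can show about 9 to 34 points in favour of continuers in 12-month status, or about 11 to 14 points against them in change from week 16. These sizes rest on assumed continuation and persistence rates; only the 40% reversal, the arm size of 70 and the 20% dropout come from the protocol. If continuation is unrelated to week-16 response and to other predictors of outcome, there is no bias. The primary randomized comparison and the sample size are not affected.

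**What to change.** 1. State that the between-arm comparison at 12 months, already planned, is the evidence on sustainability of the programme's effect.
2. Describe the continued-exercise analysis as an association and avoid causal wording when reporting it.
3. Define continued exercise and the outcome scale in advance, using the app records.
4. Stratify by week-16 Fried status or adjust for it. Add a small number of further covariates, such as baseline Fried score and app-recorded adherence in weeks 1 to 16, only if numbers allow. With roughly 21 events in the middle scenario, a long covariate list is not realistic.

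The cost is a few sentences; the Fried assessments and the app records are already scheduled. The downside is imprecision: with about 56 evaluable participants even the crude difference has a 95% half-width near 25 points in the middle scenario. Adjustment for week-16 status also leaves confounding by unmeasured health, which is why the second item is needed alongside the fourth.

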## Discussion

Multicomponent exercise is the most effective strategy for preventing pre-frailty (13). The earlier the intervention, the greater the potential benefits. However, low adherence to engagement in traditional multicomponent exercises has led to an increased sense of urgency to design new alternatives. Applying the *PF-Life* program to the pre-frail older population has multiple advantages.

First, incorporating multicomponent exercises into daily life can help older adults form exercise habits by linking training to daily tasks. Second, the *PF-Life* program is flexible and easy to adopt, with exercise equipment derived from daily life, potentially eliminating time, resource, equipment, and transportation constraints required for exercise (60, 61). Third, the *PF-Life* program is designed to be individualized according to the FF level, which is conducive to long-term adherence (62). Finally, combining evidence-based exercise for frailty prevention with behavioral technology uses emerging technologies to provide personalized interventions, feedback, and motivation, and helps people track exercise outcomes.

To explore the underlying mechanisms, the effects of lifestyle-integrated multicomponent exercise on BC and FF in pre-frail older adults will be assessed. Multicomponent exercise has been found to reduce body fat loss, increase fat-free mass, and improve physical function in both healthy and frail older adults, suggesting that BC and physical dysfunction may serve as potential markers and modifiable risk factors for frailty (63, 64) and therefore may be a key target for treating pre-frail older adults. In addition, chronic low-grade inflammation is recognized as a key factor contributing to frailty and is a hallmark of aging. It has been found that higher levels of inflammatory mediators in older populations can directly influence the onset of frailty by degrading proteins or indirectly influencing metabolic pathways, leading to frailty (6). Levels of pro-inflammatory chemokines and cytokines such as interleukin-1β (IL-1β), interleukin-6 (IL-6) and tumor necrosis factor-α (TNF-α) are known to be elevated in frail individuals, whereas levels of the anti-inflammatory cytokines interleukin-4 (IL-4) or interleukin-10 (IL-10) are reduced (65). However, there is a lack of evidence on the beneficial effects of exercise interventions based on digital technology on inflammatory levels in pre-frail older adults, particularly in terms of inflammatory biomarkers. However, physical exercise can reduce certain inflammatory biomarkers in aging older adults. Since the balance between inflammatory and anti-inflammatory biomarkers is thought to be a determinant of the severity of aging-related diseases, understanding the effects of PA on the inflammatory profile of frail and aging older adults will provide insights into the mechanisms by which exercise provides benefits and guide future customization of exercise programs for frail older adults.

To the best of our knowledge, this is the first RCT to evaluate the effectiveness of a novel and innovative digital lifestyle-integrated multicomponent exercise program in reversing pre-frailty in community-dwelling older adults and shed light on the underlying inflammatory mechanisms from a scientific perspective. The trial will use rigorous methods to reduce biases, such as randomization, active recruitment strategy, rigorous eligibility screening, innovative design of mHealth technology based on behavioral change theory, blinding of outcome assessors and data analysts, and statistical analyses based on ITT principles.

## Limitations

It is important to note that the intervention we studied was specifically designed for older adults who use smartphones. While there has been a significant increase in smartphone usage among older adults in China, particularly due to COVID-19 prevention and control measures, this still limits the generalizability of our findings to a broader population of seniors. Nonetheless, research indicates that digital technology-based interventions may be more motivating, engaging, and appealing to older adults compared to traditional methods. Furthermore, such virtual exercises could serve as an effective alternative to in-person physical activities during times when outdoor activities are restricted due to unforeseen circumstances, such as mandatory closures related to COVID-19 or adverse weather conditions (66). In addition, participants and intervention staff could not be blinded due to the difficulty of blinding in an exercise intervention. It may increase the risk that the results of the study will be influenced by the expectations of the participants and the researcher.

